## Abstract

Over recent decades, Emotion-Focused Therapy, aging, and forgiveness have garnered significant attention in the field of psychology. However, there is a lack of studies on Emotion-Focused Therapy and forgiveness specifically tailored for older adults. This article presents a protocol designed to assess the feasibility and acceptability of a randomized controlled trial of Emotion-Focused Therapy aimed at resolving emotional injuries in individuals aged 65 and older, within the context of interpersonal offenses. Feasibility will be evaluated through recruitment and retention rates, as well as adherence to the intervention protocol. Acceptability will be assessed based on perceived treatment credibility, participants’ expectations regarding outcomes, levels of engagement, and overall satisfaction with the intervention. The study is structured as a two-arm, parallel-group randomized trial with a waiting list control. We propose recruiting a sample of 70 participants, randomly assigned to either an immediate intervention group, which will receive Emotion-Focused Therapy over twelve weekly sessions, or a control group that will receive the same therapy after a twelve-week waiting period. Data will be collected in the beginning, middle, and at the end of therapy, and in two planned follow-ups (three and six months after therapy). Once this protocol is implemented, if the therapy proves to be feasible, acceptable, and shows promising results, the findings will inform a large-scale randomized clinical trial to advance the understanding of this treatment for individuals aged 65 + .

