Thus, our current paper serves as preliminary research preceding a larger study, in which we aim to design a feasibility protocol for a RCT using EFT to resolve emotional injuries in individuals over 65 years of age.

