#### Primary objectives.

a. To assess the feasibility of the therapy and assessment protocol using key evaluation indicators, including recruitment rate, retention rate, and engagement rate.b. To evaluate the acceptability of the therapy, considering the following indicators: treatment credibility and client outcome expectations, engagement, and satisfaction.

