#### Secondary objective.

a. To explore the outcomes of EFT for the resolution of emotional injury among the study’s participants, according to forgiveness and letting go measures (primary outcomes) and depression and quality of life (secondary outcomes).

The aim of our study is to develop a methodologically sound and effective protocol that may serve as the foundation for a subsequent randomized clinical trial (RCT) to test the efficacy of EFT for the resolution of emotional injuries related to interpersonal offenses, in individuals aged 65 and older. In essence, a feasibility study such as the one proposed here, functions as a tool to assess the viability of the main trial (RCT)—specifically in terms of recruitment, retention, measurements, and other parameters—without necessarily focusing on clinical outcomes [22,27–29].

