### Study setting

The research will include individuals aged 65 years or older, of all genders, who meet the study’s inclusion criteria. Therapy sessions will be conducted individually and in person, in offices suited for psychological practice. Participants residing in senior housing will have the option, subject to agreement with their institution, to have sessions conducted in their facilities [22,23]. Each session will last one hour and occur weekly over a three-month period, resulting in a total of 12 sessions per participant, in accordance with the EFT protocol for resolving emotional injuries established by Meneses and Greenberg (2019), with adaptations presented below.

At the conclusion of the designated sessions, in accordance with the study plan and study procedures (Fig 1), assessment data will be gathered in paper format. When a participant misses a session, it will be rescheduled as soon as possible. The questionnaires will be completed after the sessions. If necessary, a member of the research team will assist participants in completing them in order to prevent fatigue. In all cases, the questionnaires (with their number based on previous study protocols involving older adults [32]) will be administered in distinct and varied sessions, with clear instructions, scheduled breaks, and diverse formats to minimize fatigue — regardless of significant variations in the participants’ individual schedules [29,32]. All collected data—including attendance records and dropouts—will be analyzed in accordance with the study protocol (intent-to-treat analysis versus treatment completers analysis), not only to inform the current analysis but also to support the design of future studies. It is expected that at least 70 participants will complete the intervention (more on this below), and any reasons for dropout will be systematically documented. Regarding the secondary objective, which focuses on the analysis of outcome variables, particular attention will be given to the data from participants who complete the full intervention (completers).

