### Progression criteria

This study protocol will be developed for broader research based on the assessment of its acceptability and feasibility. Regarding the CEQ measure, the study will proceed without changes if the result is ≥ 6 on a 9-point Likert scale. The study will also progress without changes in the Session Satisfaction Module if the result is ≥ 3 on a 5-point Likert scale [22]. For recruitment, the progression criterion will be a rate of 75–100% of the sample size [61]. The criterion for retention level will be a rate >80% [36]. The progression criterion for the questionnaires will be a response rate >90%. For homework assessment, a score of ≥ 3 on a 5-point Likert scale will be required [22,29].

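### No progression criterion is specific to the waiting-list arm, and retention as defined cannot register controls lost during the 12-week wait

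*Protocol article*

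**What the plan says.** The Abstract describes "a protocol designed to assess the feasibility and acceptability of a randomized controlled trial of Emotion-Focused Therapy". The Introduction closes in the same vein: "we aim to design a feasibility protocol for a RCT using EFT to resolve emotional injuries in individuals over 65 years of age". The Secondary objective section adds that a feasibility study of this kind "functions as a tool to assess the viability of the main trial (RCT)—specifically in terms of recruitment, retention, measurements, and other parameters".

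The primary objectives are worded around the treatment: "To assess the feasibility of the therapy and assessment protocol using key evaluation indicators" (recruitment, retention and engagement rates) and "To evaluate the acceptability of the therapy, considering the following indicators".

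The Progression criteria section lists six rules:
- CEQ of at least 6 on the 9-point scale
- session satisfaction of at least 3 out of 5
- homework rating of at least 3 out of 5
- recruitment of 75–100% of the sample size
- retention: "The criterion for retention level will be a rate >80" per cent
- questionnaire response above 90%

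None names an arm. Two other sections fix what retention means. Under Intervention feasibility measures, a dropout is someone who stops therapy altogether. Under Quantitative analysis, retention is the number completing therapy relative to the number who began it.

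Controls are assessed during a three-month wait before they start the same therapy (Study design). The Participants section plans 80 recruits so that at least 35 complete each group. Study setting says that "any reasons for dropout will be systematically documented".

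**The concern.** Controls go on to receive the same therapy, so the wait supplies the only period in which randomised groups differ in treatment. Whether controls stay through it and give outcomes at its end is therefore a central feasibility question for the main trial.

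The retention rule does not address that question. A control who leaves during the wait never began therapy, so that person is not a dropout as defined and does not enter the retention ratio. The study could report satisfactory retention while the comparison the main trial depends on has lost much of one arm. If the main trial went ahead on that basis, unequal loss between arms could bias its treatment comparison.

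**Working it through.** **Inputs from the protocol.** Allocation is 35 to each arm as a minimum. Recruitment is 80, described as 15% above 70: 70 × 1.15 = 80.5, so 80 is reproduced to rounding, or 40 per arm under equal allocation. Retention is completers ÷ starters and must exceed 80%. Questionnaire response must exceed 90%.

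**Assumptions.** The protocol gives no loss rate for the wait and no therapy completion rate. I take completion among starters as 85%, with 90% as a check, and vary the loss in the wait from none to all. Counts are rounded to whole people.

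**Retention as defined.** With 35 per arm and L controls lost in the wait, starters = 35 + (35 − L). Completers = 0.85 × 35 (30 people) + 0.85 × (35 − L).

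| Controls lost in wait | Retention as defined | Same completers over all randomised | Controls kept to end of wait |
|---|---|---|---|
| 0 | 60/70 = 85.7% | 60/70 = 85.7% | 35/35 = 100% |
| 10 | 51/60 = 85.0% | 51/70 = 72.9% | 25/35 = 71.4% |
| 15 | 47/55 = 85.5% | 47/70 = 67.1% | 20/35 = 57.1% |
| 20 | 43/50 = 86.0% | 43/70 = 61.4% | 15/35 = 42.9% |
| 35 | 30/35 = 85.7% | 30/70 = 42.9% | 0/35 = 0% |

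The second column passes >80% in every row. It moves only through rounding, because loss in the wait removes people from both parts of the ratio.

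At 90% completion the picture is the same: 50/55 = 90.9% with 15 lost and 32/35 = 91.4% with all lost. With 40 per arm, 85% completion and 20 lost, retention as defined is 51/60 = 85.0%, against 51/80 = 63.8% of those randomised.

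**Would a pooled rate over all randomised be enough?** No. If the intervention arm loses nobody, 13 of 35 controls (37%) can go and the rate is 57/70 = 81.4%, a pass. The 14th loss gives 56/70 = 80.0%, a fail. The rate has to be given by arm.

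**Other criteria.** Recruitment (at least 52.5 of 70, or 60 of 80) is settled at enrolment and does not respond to later loss. Suppose questionnaire response is counted on all randomised and the intervention arm answers in full. It then fails at 7 of 35 controls lost (63/70 = 90.0%, not above 90%) and would fail clearly at 15 (55/70 = 78.6%). If it counts only forms handed out, or people still in the study, it does not react.

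**A control-arm check at >80%.** With 40 controls, 32/40 is exactly 80%, so a pass needs at least 33. The binomial probability of 33 or more is 0.958 at true completeness 90%, 0.756 at 85% and 0.055 at 70%.

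**The case against.** A reader might infer that every progression criterion concerns the therapy alone, and that the study can meet all of them with a failed control arm. The document does not support that.

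Recruitment is judged against the sample size of a two-arm randomised study, so widespread refusal of randomisation would lower it, even though the measure is loosely worded as joining the therapy. The questionnaire rule may also be a safeguard. Take 40/40 in the intervention arm and 25/40 among controls, all over 80: 65/80 = 81.3% passes a pooled retention rule but fails a >90% response rule, which needs 73 of 80.

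That safeguard cannot be presumed, because the rule states no arm, time point or denominator. The plan's own expectation of 70 completers from 80 recruits is 87.5%. If those who drop out return no forms, that would fail a >90% rule counted on everyone, so a narrower denominator may be intended.

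A reader might also see a flat contradiction between Abstract and objectives. That goes too far. Objective (a) lists recruitment and retention and covers the assessment protocol, and the Abstract itself makes progression depend on the therapy proving feasible and acceptable. The difference in wording is loose and changes no result by itself.

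Nor is the control arm ignored. Controls are assessed in the wait, 35 completers are planned in each group, missing data are measured and reasons for dropout recorded. All of this stands, but none of it is a progression criterion. Reasons for declining are participant-flow detail that an article may leave to the full protocol, so their absence is not an error.

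**Conclusion.** The point holds in this form: no progression criterion is specific to the waiting-list arm or to acceptance of randomisation, and the >80% retention rule, on the protocol's own definition, cannot respond to controls lost during the wait. It passes at 85.5% when the control arm has kept 57.1%, and at 85.7% when it has kept nobody.

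The insensitivity follows from the definition and does not depend on the assumed loss. The particular percentages rest on the assumed completion of about 85% and on 35 per arm; 90% completion or 40 per arm gives the same pattern. Whether the full set of criteria would miss a failing control arm depends on the unstated questionnaire denominator. This should be settled before recruitment starts, since it bears directly on the decision to proceed to a randomised trial.

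**What to change.** In the Progression criteria section:

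1. Judge retention and outcome completeness separately by arm, with all randomised participants as denominator. For controls, include the percentage giving both the EFI and the Letting Go Measure at the end of the 12-week wait, against the existing >80% threshold.
2. State that the >90% questionnaire rate is counted on all randomised participants, and at which time points.
3. Report descriptively how many eligible people decline because of randomisation or the wait. Without a threshold this is information for the main trial, not a progression criterion.

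The work is a few lines of text and one reason code on the screening form. Recruitment has not begun. The price is one more criterion that can fail: with 40 controls, a true completeness of 85% fails 1 − 0.756 = 24% of the time, and 90% fails 1 − 0.958 = 4%. Item 2 also makes the questionnaire rule stricter than the by-arm check when loss is even. With 4 of 35 lost in each arm, both arms pass >80% at 31/35 = 88.6%, but the pooled response of 62/70 = 88.6% fails >90%. The sponsor should adopt that denominator knowingly.

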## Introduction

Forgiveness has become a significant area of study in contemporary psychological research [1]. From a psychological perspective, we can distinguish between letting go—an emotional process through which the needs and feelings related to the offense are appropriately addressed without developing empathy towards the injurer—and forgiveness, which also involves the development of empathy or other more positive feelings, attitudes or perspective towards the injurer [2,3].

Although there is no consensual definition of forgiveness within the field of psychology [1,4], due to its multifaceted nature and diverse interpretations, we define it here as a process through which individuals address the negative emotions associated with an offense directed at them, while cultivating empathy and compassion toward themselves, the situation, and the offender [2,5]. It may encompass several stages: acknowledging the harm done, being open to the prospect of forgiveness, and nurturing the emotional, cognitive, and behavioral components essential for forgiveness [1,4].

Forgiveness is not the only path to emotional resolution; other approaches, such as letting go of resentment or validating emotions like anger, may also be effective [1,6,7]. In this context, resentment can be a response—among other possible reactions—to unjust and offensive situations. However, it can become detrimental and chronic if it persists and intensifies over time [1,2,8]. Following an offense, the absence of an adequate or adaptive response may leave the victim with unmet needs, such as the need for protection, support, and understanding [2]‌‌. Simultaneously, maladaptive responses may emerge, including silence, rumination, or aggression, which can develop into entrenched maladaptive patterns [2,8,9]. Such chronic resentment may lead to maladaptive behaviors, thoughts, and feelings, hindering a person’s ability to respond appropriately to the offensive experience [10,11].

Considering that forgiveness can be approached from the perspective of the victim, the offender, or through self-forgiveness, the present study focuses specifically on forgiveness from the perspective of the offended individual [4]. In light of the points discussed thus far, the study of forgiveness in older adults emerges as highly justified for several reasons. The ability to forgive develops and evolves over a person’s lifetime [12,13], even though only 5% of forgiveness research has included older adults in their samples [5]. This stage of life provides a valuable opportunity to address and resolve long-standing issues, particularly through processes of meaning reconstruction [6,14]. In fact, various scholars highlight that forgiveness can serve as a crucial resource throughout one’s life, helping to resolve interpersonal problems and contribute significantly to healthy aging [12,14]. Specifically, research has demonstrated that forgiveness offers a range of benefits during the aging process, with meaningful impacts across various dimensions of health [1,4].

At the physical level, forgiveness has been linked to a reduced risk of cardiovascular disease and to the enhancement of both endocrine and immune system functioning [1,14]. From an emotional perspective, it is associated with increased subjective well-being and lower levels of anxiety and depression [4,13]. Socially, forgiveness facilitates reconciliation with the past, fosters the development of empathy, and promotes stronger interpersonal relationships [1,13]. These benefits are frequently connected to reductions in stress, improvements in physical and psychological functioning, and enhanced social engagement—all of which are key components of successful aging [13,15]. Thus, forgiveness holds the potential to reduce the negative health effects of unresolved transgressions, playing a pivotal role in promoting well-being and resilience in older adulthood [14,13].

Forgiveness assumes a special relevance in later life, particularly in the context of resolving emotional injuries [6]. One contributing factor is the increased openness often observed with advancing age—manifested in a greater willingness to release resentments and to both extend and accept forgiveness. Scholars have noted that such tendencies are linked to indicators of positive aging and are inversely associated with signs of psychological and existential decline in late life [5,13]. At the same time, factors such as diminished social networks, growing physical frailty, the cumulative effects of individual life trajectories, and unresolved personal adversities may call for tailored consideration when addressing forgiveness processes in this demographic [4,6].

Indeed, several studies indicate that forgiveness has unique implications for older adults [13]. López et al. (2021) conducted a meta-analysis focusing on the effectiveness of forgiveness therapies among older adults, covering studies published from 1990 to 2020. Their analysis revealed that participants who underwent forgiveness therapies reported higher levels of forgiveness compared to those who did not [13]. Furthermore, these therapies were found to be negatively associated with levels of depression, stress, and anger, while being positively associated with indices of life satisfaction, subjective happiness, and psychological well-being [5,13].

Conversely, Webster et al. (2021) found that the severity of emotional injury resulting from transgressions is positively associated with a decline in the quality of physical health in older adults. Thus, forgiveness can diminish the adverse effects of transgressions on health, playing a significant role in successful aging [12,14]. Research by Toussaint et al. (2015) indicates an inverse correlation between forgiveness and markers of end-of-life health conditions, including cardiovascular, endocrine, and immune system functioning. Consequently, forgiveness has increasingly been recognized as a potential resource for promoting psychological well-being and longevity in later life, due to its positive associations with overall health and quality of life [12–14].

The growth of studies on forgiveness in older adults, along with increasing recognition of its positive impact, has paralleled the expansion of research on aging—driven by several factors, including the growing older population and advances in their quality of life [15]. Aging is a multifaceted process of personal development characterized by both gains and losses, influenced by various age-specific internal and external factors, individual traits, and the surrounding context [15,16]. This multifaceted process encompasses aspects such as fostering healthy lifestyles, acknowledging and adapting to inevitable losses, optimizing individual capabilities, and cultivating self-compassion [15].

Therefore, it is essential to understand aging as a multidimensional process involving the dynamic interaction of biological, psychological, and social components. Biological aging encompasses natural, progressive, and irreversible physiological changes [15]. Social aging reflects the roles, norms, and expectations shaped by cultural and societal contexts. Psychological aging includes not only potential cognitive decline but also gains in emotional regulation, accumulated knowledge, and self-awareness [15]. Aging is commonly categorized into three types: primary (normal), secondary (pathological), and tertiary (terminal) [16–18].

Contemporary gerontology increasingly adopts positive conceptual frameworks—such as successful, active, and healthy aging—which emphasize autonomy, social participation, and quality of life [15]. The World Health Organization (WHO) defines healthy aging as the process of developing and maintaining functional ability [18]. Psychological theories, ranging from Erikson’s stages of psychosocial development to more recent models like Gerotranscendence, underscore the developmental and transformative potential of aging [16,17]. Ultimately, aging well involves resilience, self-compassion, life satisfaction, social support, and living in accordance with one’s values [17].

Aging can involve psychosocial difficulties such as social isolation, loneliness, memory lapses, elder abuse, and dementia [17]. Moreover, the psychological well-being of this population is closely linked to autonomy, personal growth, self-acceptance, environmental control, health promotion, life goals, psychological care, and social relationships [15]. According to Erikson (1963), around age 65, individuals confront the final crisis: integrity versus despair. So, this period can be characterized by deep reflection, acceptance, and the integration of past events into a meaningful whole. Despair may manifest as an inability to reconcile life’s difficulties [18]. Given the above, we might hypothesize the significant role that forgiveness can play in fostering physical, mental, and emotional well-being as individuals age [1,4,15].

Although forgiveness may be associated with beneficial outcomes in adults over the age of 65, these results are not inherently assured. It is also important to consider the potential for pseudo-forgiveness and misunderstandings surrounding the concept of forgiveness [6,14]. Band-Winterstein et al. (2024), for instance, remind us that elder abuse—one of the primary psychosocial difficulties that tend to arise in aging [17]—involves a breach of fundamental trust and tends to be associated with specific feelings (anger, fear, sadness, revenge), thoughts (hostility, loss of respect for the aggressor), and behaviors (minimizing or engaging in aggressive actions, avoidance). Therefore, it is essential for individuals, in the process of forgiveness, to be aware and free to fulfill their fundamental psychological needs [4,6,14].

Concerning this, previous exploratory studies conducted by our research team [18,19] suggest that individuals over the age of 65 face specific challenges in the forgiveness process, including internal conflicts, rationalization, vulnerability, denial, and avoidance. These difficulties are often interrelated and interact in a dynamic way [18,19].

In light of these considerations—particularly the recognition of the harmful consequences of chronic resentment and the positive impact of therapeutic approaches in addressing such emotional injuries—there is substantial evidence supporting the benefits and positive outcomes of forgiveness-focused therapies [1,5]. Fundamentally, these interventions aim to enhance emotional well-being by addressing the emotional injuries resulting from interpersonal offenses. Specific interventions actively foster forgiveness, as exemplified by the REACH Forgiveness model [1] and the Enright Process Model of Psychological Forgiveness [4]. These two therapeutic models constitute the main pillars of forgiveness-related studies and interventions. The first model, which emphasizes the crucial distinction between the decision to forgive and the emotional process of forgiving, can be summarized in five key stages: recall the hurt (R), empathy (E), altruism (A), commitment (C), and holding onto forgiveness (H), under the acronym REACH [1]. The second model is characterized by its emphasis on the moral development of forgiveness-related reasoning and is structured into four main stages: uncovering, decision, work, and deepening [4]. Conversely, other approaches integrate forgiveness as one potential avenue for addressing emotional injuries. For instance, Emotion-Focused Therapy (EFT) presents the option of letting go—without necessarily involving forgiveness—as a viable strategy for healing emotional wounds [2,3].

A previous meta-analysis examining the effectiveness of psychotherapeutic interventions in promoting forgiveness [9] revealed that participants who underwent forgiveness-focused interventions experienced significantly higher levels of forgiveness compared to those who received no therapy and those undergoing alternative therapies. This meta-analysis conducted by Wade et al. (2014) highlighted not only the positive effects of forgiveness on well-being—such as reductions in anxiety and depression—but also demonstrated that the longer forgiveness-focused therapy is implemented, the greater are its benefits, with these positive effects tending to persist over time [9]. In addition, the analysis indicated that individually delivered interventions generally produce more favorable outcomes than group-based approaches [9]. Furthermore, the studies analyzed by Wade et al. (2014) indicated that EFT was one of the therapies with very positive results for resolving the emotional injury caused by an offense, as evidenced by the primary forgiveness measure (e.g., Enright Forgiveness Inventory–EFI) [10].

Therefore, it becomes clear that there is a need to develop new therapeutic approaches specifically tailored to adults aged 65 and older, thereby expanding the range of evidence-based interventions available for this population. In this context, EFT emerges as a promising approach, as suggested by Wade’s meta-analysis and its demonstrated effectiveness in other settings, and particularly due to its flexibility in addressing both *letting go* and forgiveness [9,11]. However, despite existing studies on EFT and forgiveness, this approach has not yet been tested with older adults [1,2].

Meneses and Greenberg (2019) propose an EFT protocol for the resolution of emotional injuries, which has been found to facilitate the forgiveness process by transforming painful feelings, thoughts, and actions into empathy, compassion, and love. The approach proposed by these authors involves five phases: establishing a therapeutic alliance; exploring emotions using chair work such as the empty-chair task; addressing self-interruptions through two-chair work; promoting forgiveness or letting go via emotional transformation; and concluding with strategies to reinforce emotion regulation and prevent relapse. The intervention was delivered over twelve weekly sessions [2]. According to EFT, therapeutic change occurs through activating painful emotions and memories and changing clients’ emotional experiences [3,7]. So, accessing disowned painful feelings related to the offense, including sadness, anger, and resentment, is crucial [5,8].

Now, EFT is highly effective for resolving internal conflicts by focusing on empathic attunement and emotions as central to therapy [2,3]. By accessing core primary emotions, it helps restructure painful experiences and their meanings, allowing for new emotional experiences to emerge [2,20]. This dynamic process adapts to individual needs, facilitating the resolution of unresolved conflicts [20,21].

Indeed, a variety of reasons—such as the need for an integrated understanding of forgiveness and aging, the scarcity of studies on forgiveness among older adults, the potential benefits of forgiveness, and the absence of EFT studies for older adults—justify exploring the impact of EFT applied to resolving emotional injuries in individuals over the age of 65.

Given all that has been mentioned so far, the importance of a study protocol in this context becomes clear, as it offers access to emerging research and guides the practical application of the findings [22,23]. Protocols can assist in outlining and justifying the research objectives, methods, participant criteria, interventions, and data collection, ensuring alignment with the study’s goals [24]. They support rigorous implementation, replicability, and efficiency while upholding scientific integrity, ethical standards, participant protection, and facilitating ethical approvals [25,26].

Thus, our current paper serves as preliminary research preceding a larger study, in which we aim to design a feasibility protocol for a RCT using EFT to resolve emotional injuries in individuals over 65 years of age.

